Deduced to the specific objectives we assume that increased exposure to wastewater and faecal sludge results in higher infection rates of parasitic diseases and other water-related diseases outcomes. Therefore we intent to test following two hypotheses:

1. The difference in odds ratio is 2.5 or higher between highly exposed groups (people working along the wastewater and faecal sludge chain) and the people without an exposure to the two waste chains (control groups).
2. The helminth infection intensity decreases with the distance to wastewater treatment plant in Bugolobi and the Nakivubo swamp.
3. Methodology
   1. Study site

Kampala is the capital and largest city of Uganda with a resident population of 1,597,500 people who live on an area of 197 km² (UBOS, 2010). This population nearly doubles during the day due to people who live in the neighbouring areas and travel to Kampala on a daily basis. The city has a [tropical climate](http://en.wikipedia.org/wiki/Tropical_wet_and_dry_climate) but because of the high altitude (1,190 m above sea level) the average temperature (16°C -28°C) is relatively cool compared to other lower altitude East African settings. The main rain season is between March and May and the short rain season is between November and December. Rainfall ranges between 500 mm and 2500 mm and the relative humidity is between 70% and 100% (Figure 1) (IWMI, 2012a).

The specific study site will be around the WW and FS treatment plant BSTDW and the Nakivubo swamp. It is located in an urban context of Kampala and surrounded by high density neighbourhoods in between Nakawa and Makindye divisions. The plant is operated by the NWSC and was constructed prior to the 1940s by the British and subsequently extended during the periods of 1956/1958. The WW entering the plant is treated via primary (grit and detritus removal and primary sedimentation), and secondary processes (effluent: trickling filter system secondary sedimentation; and WW sludge: anaerobic digestion ponds and drying beds). The secondary treated effluent is then led through a natural wetland (Nakivubo swamp) where it is tertiary treated before it is discharged into Lake Victoria (Figure 2). There are plans that the BSTDW is put out of service within the next 4-6 years, and replaced by a new plant. At the moment, NWSC and KCCA are conducting studies to determine the most appropriate treatment processes for this context.

[figure not shown]

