Further, we will conduct with each participant a questionnaire interview (will take about 30 min) to assess e.g. their demographic, occupation, intensity and causality of exposure to WW and FS, personal protective equipment, hygienic behaviour and signs and systems of specific health outcomes (ANNEX 10.1). Later, each participant will be provided with a small plastic container which is labelled with their unique ID. Participants will be invited to return the container with a fresh morning stool sample the following day directly to the working place for W1 and W2 and for community member and farmer to an appointed health centre. The anticipated study period for W1 will be 2 days, for W2 5 days, for F 10 days, for C1 5 days and for C2 10 days.

Table 6 Sampling framework for the cross-sectional study

| Exposure group | Total participants | Allocated working days | Selected unit | Participants per unit |
| --- | --- | --- | --- | --- |
| **Worker 1** | 50 | 2 | Excessive sample | 50 workers |
| **Worker 2** | 100 | 10 | Excessive sample | 100 workers |
| **Farmers** | 275 | 10 | 275 randomly selected farmers from pre-compiled list |  |
| **Communities 1** | 225 | 5 | 9 squares (1km^2^) | 25 households (one member per household) |
| **Communities 2** | 350 | 10 | 14 squares (1km^2^) | 25 households (one member per household) |

- - - 1. Inclusion and exclusion criteria

Wastewater treatment plant workers, faecal sludge workers, farmer and community members will not be allowed to participate in the study if they do not fulfill any of the following exclusion criteria:

- too sick to attend school or participate in the study (e.g. severe diarrhoea, severe anaemia, high fever, etc.)
- absence of written informed consent
- person is younger than 18 years of age
  - - 1. Sample analysis

The collected stool samples will be transferred to the laboratory of the Vector Control Division of the MOH on the same day for examination of helminth eggs and intestinal protozoa cysts.

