For each stool sample duplicate Kato-Katz thick smears will be prepared, using standard 41.7 mg template. The slides will be labelled with the participants unique ID plus ether ‘A’ (first Kato-Katz) or ‘B’ (second Kato-Katz) and allowed to dry for at least 30 minutes. Slides will be examined quantitatively under a light microscope by 1 laboratory technicians. For each slide the number of helminths (*A.lumbricoides*, hookworm, *T.trichiura* and *S.mansoni* and other helminth) will be counted and recorded separately.

Additionally, for each stool sample we will perform a FECT to detect protozoa infections. In short, approximately 1 g of the stool will be placed in a tube containing 10 ml of formalin and labelled again with the unique ID number of the participant plus a C. The sample will be mixed, centrifuged and the supernatant removed. 7 ml saline solution will be added, mixed and centrifuged. The sediment is the examined on presence of helminth eggs and intestinal protozoa cysts under a light microscope.

For quality control 10% of all the Kato-Katz slides will be re-examined by an external person (e.g. PhD student), the results of the *A.lumbricoides, T.trichiura* and *S.mansoni* egg counts compared and any discrepancies removed by re-examining the discordant slides.

A subset of the stool samples (100-150 samples) will be frozen (-20°C) and transferred to Swiss TPH in Switzerland for pending polymerase chain reaction (PCR) for species detection and/or meta-genomic analysis in order to provide quantitative insights into microbial population based on sequence data.

- - - 1. Study variables for the cross sectional survey
         1. *Dependent variables*

As dependent variables we will measure the prevalence of all detected parasitic infection (helminth and intestinal protozoa) and the intensity of helminth infections in the stool samples. For the questionnaire study we will ask the participants questions about symptoms and signs of certain disease outcomes to estimate the prevalence of fever and skin, eye, reparatory diseases and diarrhoea episodes within a two week recall period.

- - - - 1. *Independent variables*

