Investigators will ensure that the study will be conducted according to the study protocol, with good epidemiological practice and the applicable regulatory requirements. Any protocol amendments will be submitted for review to the ethics committees for each study partner. As participant safety is a primary concern, any unforeseen event posing a risk to the participants will be communicated to the ethical committees. The investigators have sufficient time to properly conduct and complete the study within the agreed timeframe and have available an adequate number of qualified staff and adequate facilities for conducting the research properly and safely. Informed consent will be obtained from each participant and documented, and the version approved by the ethics committee will be adhered to. The investigators will ensure the accuracy and completeness of the data reported in the study, and will timely submit the required progress and final reports.

1. Collaboration and support

The PhD thesis is embedded in the larger RR&R project which is financed by the Swiss Agency for Development and Cooperation (SDC) and carried out within the frame of an existing research partnership between: (i) SOPH; (ii) MOH; (iii) NWSC; and (iv) the Department of Civil & Environmental Engineering of Makarere University in Kampala, Uganda and internationally: (i) the Swiss TPH (Basel, Switzerland); (ii) IWMI (Colombo, Sri Lanka); (iii) WHO (Geneva, Switzerland); (iv) the International Centre for Water Management Services (CEWAS) (Willisau, Switzerland); and (v) SANDEC (Dübendorf, Switzerland).

1. Time table

The following activities are planned within 3 months between August and October 2013.

| **Months** | **Mai-July** | **August** | | | | **September** | | | | **October** | | | |
| --- | --- | --- | --- | --- | --- | --- | --- | --- | --- | --- | --- | --- | --- |
| **Weeks** | **18-31** | **32** | **33** | **34** | **35** | **36** | **37** | **38** | **39** | **40** | **41** | **42** | **43** |
| Health risk assessment (HRA) SOPH and Swiss TPH |  |  |  |  |  |  |  |  |  |  |  |  |  |
| Follow up visit HRA  (community group discussion) |  |  |  |  |  |  |  |  |  |  |  |  |  |
| Preparation of field and laboratory work  **(3 days)** |  |  |  |  |  |  |  |  |  |  |  |  |  |
| Training workshop with field staff and lab staff **(1 days)** |  |  |  |  |  |  |  |  |  |  |  |  |  |

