| Information and awareness campaign of study groups W2, F, C1, C2 **(2 days)** |  |  |  |  |  |  |  |  |  |  |  |  |  |
| Pilot testing of questionnaire and stool sample collection (**1 days)** and discussing problems and issues (**1 days)** |  |  |  |  |  |  |  |  |  |  |  |  |  |
| Interview and stool collection and analysis of **(W1) (2 days)** |  |  |  |  |  |  |  |  |  |  |  |  |  |
| Discussing issues problems **(1 day)** |  |  |  |  |  |  |  |  |  |  |  |  |  |
| Organizing data collection for W2 **(1 days)** |  |  |  |  |  |  |  |  |  |  |  |  |  |
| Interview and stool collection and analysis of **(W2)** |  |  |  |  |  |  |  |  |  |  |  |  |  |
| Organizing data collection for F, C1 and C2  **(5 days)** |  |  |  |  |  |  |  |  |  |  |  |  |  |
| Interview and stool collection and analysis of farmers **(F) (10 days)** |  |  |  |  |  |  |  |  |  |  |  |  |  |
| Interview and stool collection and analysis of control groups **(C1) (5 days)** |  |  |  |  |  |  |  |  |  |  |  |  |  |
| Interview and stool collection and analysis of control groups **(C2) (10 days)** |  |  |  |  |  |  |  |  |  |  |  |  |  |
| Starting WW and FS analysis **(1 day)** |  |  |  |  |  |  |  |  |  |  |  |  |  |
| Lab analysis for WW and FS by NWSC  **(over 2 month each week 2*16 samples)** |  |  |  |  |  |  |  |  |  |  |  |  |  |
| Buffer time |  |  |  |  |  |  |  |  |  |  |  |  |  |

Estimated budget

| **Estimated inventory needed for PhD study** | **Number** | **Unit** | **No. units** | **Total No.** | **Amount per unit**  **CHF** | **Total CHF** |
| --- | --- | --- | --- | --- | --- | --- |
| **PhD personal costs** | | | | | | |
| Flight | 1 | Flight | 1 | 1 | 1'200 | 1,200 |
| Accommodation | 1 | Month | 3 | 3 | 600 | 1,800 |
| Other expenditure (internet, printing) | 1 | Month | 3 | 3 | 100 | 300 |
| **SOPH** | | | | | | |
| **Already covered under TOR for Phase 1** | | | | | | |
| Assistance with the planning of potential epidemiological studies and/or exposure (e.g. ethical clearance procedures, coordination between partners (SoPH, MoH and NWSC) and arrangements for of sampling and data collection) | | | | | | |
| Letter of agreement for phase 1 (includes 2 BSc students + 1 senior person) | 6 | Month | 1 | 6 |  | 10,670 |
| Phase 2 | | | | | | |
| BSc student Field staff (sample collection and interviews) | 2 | Month | 3 | 6 | 400 | 2'400 |
| Transport | 8 | Week | 1 | 8 | 50 | 400 |
| Ethical clearance (Uganda) | 1 | Clearance | 1 | 1 | 700 | 700 |

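### Workers are surveyed before communities in separate blocks of field days, so exposure group is confounded with calendar time, mainly for the two-week symptom outcomes

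*Combined protocol and SAP*

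**What the plan says.** Section 4.2.1.3 (Sampling procedures) allots field days by exposure group: "The anticipated study period for W1 will be 2 days, for W2 5 days, for F 10 days, for C1 5 days", and 10 days for C2. Table 6 in the same section repeats the allotment but disagrees on W2: "Worker 2 | 100 | 10 | Excessive sample", that is 10 days against 5 in the text.

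Section 7 (Time table) has one row per group. After training, a pilot and a discussion of problems, the rows are:

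- W1 (2 days)
- a discussion day
- "Organizing data collection for W2" (1 day)
- W2
- "Organizing data collection for F, C1 and C2" (5 days)
- F (10 days), C1 (5 days) and C2 (10 days)

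The window is fixed: "The following activities are planned within 3 months between August and October 2013". The bars showing which weeks each row occupies are not in the text.

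Section 4.2.1.6.1 takes symptoms, including "diarrhoea episodes within a two week recall period", from the questionnaire. Section 4.2.1.5 sends stool to the laboratory on the day it is collected, so slide reading is likely to follow survey order. It also states: "Slides will be examined quantitatively under a light microscope by 1 laboratory technicians". Ten per cent of the Kato-Katz slides are re-read by an external person.

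The confounders in sections 4.2.1.6.2 and 4.2.1.7.2 are demographic, behavioural, dietary and socio-economic. Section 4.2.1.8.2 specifies multilevel regression adjusted for confounding. None of these names interview date, reading date or a calendar term, and nothing provides for mixing groups within days or weeks.

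**The concern.** Hypothesis 1 contrasts the most exposed people with unexposed controls, and the sample size section makes that W1/W2 against C2. If workers are interviewed in one part of the field period and C2 in another, the groups report on different fortnights. A change over those weeks in background diarrhoea, fever, or skin, eye or respiratory illness, or in how the assistants interview, would then look like an effect of wastewater or would hide one.

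Stool results are less exposed. The route there is not a change in infection but a gradual change in how slides are read. Once the data have been collected in blocks, the analysis has little with which to tell time from exposure.

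**Working it through.** **1. The plan's own allowance for adjustment (section 4.2.1.2).** The plan lets confounders remove 35% of exposure variance. √0.65 = 0.806 and 1/0.806 = 1.24 (the plan uses 1.25). (1.96 + 0.84) × 1.25 = 3.50 = 1.96 + 1.54, and Φ(1.54) = 0.938, slightly under 95% as stated. So 65% of exposure variance must remain.

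**2. Days in row order.** Working days are counted from the first W1 day, with W2 at 5 days (at 10 days in brackets).

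| Step | Days |
|---|---|
| W1 | 1–2 |
| Discuss problems, organise W2 | 3–4 |
| W2 | 5–9 (5–14) |
| Organise F, C1, C2 | 10–14 (15–19) |
| F | 15–24 (20–29) |
| C1 | 25–29 (30–34) |
| C2 | 30–39 (35–44) |

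All listed tasks end to end take 3+1+2+2+2+1+1+5+5+10+5+10 = 47 working days (52 with W2 at 10). Weeks 32–43 give 12 × 5 = 60, so the sequential layout fits.

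**3. Recall windows.** From the last W1 day (2) to the earliest possible community day (15) is 13 working days, at least 17 calendar days. Those 14-day windows do not overlap on any reading. From the last W2 day (9) to day 15 is 6 working days, or 8–10 calendar days, so those windows can overlap if communities start at once. In row order, the last worker day and the first C2 day are 30 − 9 = 21 working days apart, at least 29 calendar days, with no overlap.

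**4. Share of exposure variance explained by survey day.** Scores are W = 1, F = 2/3, C1 = 1/3, C2 = 0. Sizes are W1 50, W2 100, F 275, and C1/C2 either 225/350 (Table 6) or 350/225 (section 4.2.1.2), because the documents differ. Participants are spread evenly over their days, and R² = Cov²/(Var score × Var day).

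Example with W2 at 5 days and C1/C2 at 225/350. The mean score is 0.408 and its variance 0.1305.

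- Row order: the group mean days are 1.5, 7, 19.5, 27 and 34.5. Cov = 6.375 − 0.4083 × 24.29 = −3.54 and Var day = 106.1, so R² = 12.55/13.85 = 0.91.
- F, C1 and C2 all starting on day 15: Cov = 5.625 − 0.4083 × 16.79 = −1.23 and Var day = 31.7, so R² = 1.51/4.13 = 0.37.

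Over both W2 lengths and both C1/C2 sizes, R² is 87–91% in row order, leaving 9–13%. In parallel it is 36–39%, leaving 61–64%, just under the 65% the plan allows for. Mean W and C2 dates are 29–33 working days apart in row order and 14–18 in parallel.

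**5. What adjustment would cost.** The documents give no symptom prevalences, so this uses the plan's parasite figures (20% in C2, odds ratio 2.5, ln 2.5 = 0.916).

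- Without a day term the standard error is 0.198 or 0.216, depending on the C1/C2 sizes, and power is about 99%.
- In row order a linear day term multiplies the standard error by 2.8–3.3. At the low end, 0.216 × 3.21 = 0.69, 0.916/0.69 − 1.96 = −0.63, and power is 26%. At the high end, 0.198 × 2.87 = 0.57, 0.916/0.57 − 1.96 = −0.35, and power is 36%. Block indicators instead of a linear term would be fully aliased with group.
- In parallel the multiplier is 1.27–1.30 and power is 91–95%, but only if the trend is linear, because no worker shares a survey date with any community member.

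**6. Can F, C1 and C2 run together?** Four assistants and 30-minute interviews give F 27.5, C1 45 and C2 35 interviews a day, or (27.5 + 45 + 35) × 0.5/4 = 13.4 hours each. With C1 at 350 and C2 at 225 it is 15.0 hours. F with C2 alone needs 7.8 or 6.3 hours. All figures are before travel.

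**The case against.** The strongest reply is that much of the apparent size depends on timetable bars that are not in the text. F, C1 and C2 share one organising row, which is compatible with overlapping fieldwork, and F with C2 could be staffed. C2 could then start straight after the organising days. That stands: a reader might infer that C2 is surveyed last, six or more weeks after W1, and that no recall windows overlap, but the documents establish only that workers come first. Complete inseparability likewise holds only for row order.

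A reader might also infer that procedures are first tried out on W1. They are not. The timetable lists a pilot and a problem discussion before W1, and section 4.2.1.7.3 describes the pre-test. The discussion day after W1 is an extra.

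Nor do the documents show any time trend. Section 4.1 says: "The main rain season is between March and May and the short rain season is between November and December". Both seasons lie outside August to October. That limits seasonal change but does not exclude outbreaks or interviewer learning.

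The egg-count route is weak. The laboratory staff are already qualified, a single reader would remove differences between readers, and the wording may mean one reader per slide. The 10% re-read is a real but partial check: no balance by group or date is stated, and hookworm is not among the species named for comparison.

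It is also tempting to assume a rise in diarrhoea and set the resulting odds ratio beside the design value of 2.5. That value was chosen for intestinal parasitic infection, so the comparison would mislead.

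None of this removes the separation of workers from communities, or the absence of a date term.

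**Conclusion.** The point holds as an avoidable risk of bias. On any natural reading of the allotment and the preparation rows, both worker groups are surveyed before C2, so the hypothesis 1 contrast is confounded with calendar time. It matters mainly for the two-week symptom outcomes.

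Survey day explains 87–91% of exposure variance if the blocks follow row order, and later adjustment then cannot usefully separate time from group. If F, C1 and C2 run in parallel, which is hard to staff, it explains 36–39%, and adjustment is possible only by assuming the shape of the trend. These figures assume a five-day week, an even spread of interviews within blocks and equally spaced exposure scores.

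The size of any actual bias is unknown, and a reader should not take this as evidence that the results will be biased. It is a cheap improvement to make before fieldwork, not a defect that invalidates the design.

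**What to change.** - Once the farmer listing and square mapping are done, spread the W1 and W2 interviews over the same weeks as F, C1 and C2. If the 10 + 5 + 10 = 25 field days are used, that is 150/25 = 6 workers a day.
- Visit the C1 and C2 squares in one random, mixed order instead of all C1 and then all C2.
- Record interview date and slide-reading date for every participant, and include survey week in the multilevel models. With the groups interleaved over the whole field period, survey day explains almost none of the exposure variance, so this term costs little power.
- Reconcile the W2 field days: 5 in the text of section 4.2.1.3, 10 in Table 6.

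The cost is rescheduling, a later start for the workers and somewhat more travel for the four assistants. No extra participants, staff or tests are needed.

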As independent variables we ask the participants questions around their perceived exposure risk to WW and FS, their occupation, their working procedures, the personal protective equipment they use to reduce the exposure and their hygienic behaviour. To check for confounder we also ask the participants about demographic parameters (e.g. age, gender), behaviour, consumption of water and root and leaf crops and socio-economic status (ANNEX 10.1).

- - - 1. Data collection
         1. *Training of research assistants*

To accomplish the questionnaire survey, the stool sampling and we will train 4 local research assistants on the interview procedure and on the usage of the tablet computer.

To conduct the laboratory analysis we intend to collaborate with the already qualified staff of the lab of the MOH and the laboratory of the NWSC.

- - - - 1. *Tools: study questionnaire*

The questionnaire will be developed in English on paper (ANNEX 10.1) and later translated by the local partners from SoPH into the local language. Further, the questionnaire will be translated into the program code of an open-source software called Open Data Kit (ODK) (<http://opendatakit.org>), which enables us to conduct the questionnaire survey with tablet computer devices. Hence, after pre-testing we will adjust and refine the questions and the questionnaire tool to the local context.

The questionnaire interview will last for about 30 minutes and comprises of the following 10 chapters:

1. **Background information**: (i) to get information on the location of living and working, directly measured with the GPS tracking function of the table computer and later mapped with the ESRI *ArcGIS* 10 computer programme; (ii) to obtain information about potential confounding factors: gender, age and religion and ethical affiliation of the participant.
2. **Occupational back ground information:** to assess (i) information on the exposure due to occupation we ask questions to about their occupation and the exposure to Nakivubo swamp and/or channel (only for the groups C1 and C2); (ii) the intensity of occupational related exposure information around the employment, employer, function and responsibilities and working days/hours of the current occupation; and (iii) the potential positive effect on health due to received safety training and regular health check-ups.

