3. **Socio-economic status:** to assess the socio economic status as potential confounding factor we will obtain information around the salary per month, amount of people living in the household and on property possession.
4. **Hygienic behaviour:** to assess personal hygienic behaviour as potential confounding factor we will ask questions around washing/showering and hand washing.
5. **Consumption of water and food:** to assess the consumption of contaminated food and water as potential confounding factor we will obtain information around: (i) consumption and treatment of drinking water from various sources; (ii) consumption and concerns of root and leaf crops; and (iii) if participant is undertaking any farming what kind of crops he/she is growing.
6. **Disease signs and symptoms:** to observe signs and symptoms of diseases participants experienced over the past 2 weeks we will ask questions: (i) about general diseases symptoms (headache, fever, abdominal pain, acute and chronic coughing, chest pain, loss of weight, nausea, vomiting), physical pains (back, joint and muscle pain) and injuries, (ii) we will ask more specific questions around water-washed infection to determine skin and eye diseases as defined in the ‘Oxford handbook of tropical medicine’ (Eddleston et al. 2012). For skin diseases we will also ask for the specific part of the location (e.g. arm and leg); and (iii) questions on diarrhoeal episodes (defined as three or more loose or liquid stools per day) experienced today, 48 hours ago, 7 days ago and 14 days ago. Additional questions will be asked in order to characterize the diarrhoea such as presence of blood and mucus.
7. **Risk perception:** to assess the awareness of the health risk due to the work and the exposure to wastewater and faecal sludge.
8. **Personal protective equipment (PPE) (only W1/W2 and F):** to assess the use, the compliance and the efficacy of specific PPE.
9. **Worker safety (only W1/W2 and F):** to assess the need for other PPE and measures/controls that should be in place for making the work safer.
10. **Stool collection:** At a this stage of our research we want to ask the participant if he/she is willing to provide a stool sample for assessing the burden of intestinal parasites (e.g. soil-transmitted helminth and intestinal protozoa). If yes, we would measure the weight and height to calculate the body mass index to provide the appropriate dose of treatment in case of positive laboratory analysis.

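### Self-reported two-week symptoms are asked after exposure-related questions that differ by group; moving them forward is a free safeguard against differential reporting of unknown size and direction.

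*Combined protocol and SAP*

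**What the plan says.** Section 4.2.1.6.1 makes the symptoms dependent variables. The questionnaire is used "to estimate the prevalence of fever and skin, eye, reparatory diseases and diarrhoea episodes within a two week recall period". Section 4.2.1.8.2 then relates the disease outcomes to exposure by multilevel regression and compares the exposure groups by odds ratios. It does not separate stool outcomes from symptoms.

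Section 4.2.1.7.2 says the interview "comprises of the following 10 chapters". In the order listed:

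- Chapter 2 covers occupation and "the exposure to Nakivubo swamp and/or channel (only for the groups C1 and C2". It continues with intensity of occupational exposure, safety training and health check-ups, with no group restriction stated.
- Chapter 4 covers hygiene. Chapter 5 includes "consumption and concerns of root and leaf crops", plus the crops grown by anyone who farms.
- Chapter 6 covers symptoms: "to observe signs and symptoms of diseases participants experienced over the past 2 weeks we will ask questions".
- Chapter 7 serves "to assess the awareness of the health risk due to the work and the exposure to wastewater and faecal sludge". Chapters 8 and 9 (protective equipment and worker safety) are for workers and farmers only.

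The timetable in section 7 lists an "Information and awareness campaign of study groups W2, F, C1, C2", above the interview rows. W1 is not named there, and the content is not described. Under section 4.2.1.3, W1 and W2 are both sensitised through their representatives, and every selected participant is told the study's objectives and potential risks. The first digit of the participant ID codes the exposure group.

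**The concern.** A two-week symptom history depends on what the respondent recalls and thinks relevant. A person who has just answered questions about contact with polluted water, or about the hazards of the job, may search memory harder or count a milder complaint. If this happens equally in all groups, it adds noise. If it happens more in some groups than in others, it shifts the odds ratio even where disease does not differ.

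Here the questions asked before the symptoms are not the same in every group. The interviewer also knows the group, and the plan describes no masking, negative-control symptom or similar check. At stake is how the symptom odds ratios for workers and farmers against C2 can be read. The stool results do not depend on question order.

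**Working it through.** **Step 1: who is cued about what before chapter 6.**

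| Asked before symptoms | W1, W2, F | C1 | C2 |
|---|---|---|---|
| Swamp/channel contact (ch. 2) | no | yes | yes |
| Occupational exposure, training, check-ups (ch. 2) | yes, about waste-related work or farming in the swamp | yes, about their own job | yes, about their own job |
| Hygiene (ch. 4), crop concerns (ch. 5) | yes | yes | yes |
| Crops grown (ch. 5) | if farming | if farming | if farming |

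Two differences run in opposite directions. The swamp items cue the control group C2 and not the workers or farmers, which would lower the worker and farmer odds ratios against C2. The occupational items remind workers and farmers of waste contact, which would raise them. The net sign cannot be read from the text.

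**Step 2: what a differential could do.** The plan gives no figure for reporting error, so the values here are assumptions. With true prevalence p, sensitivity Se and specificity Sp, the observed prevalence is p·Se + (1 − p)(1 − Sp). The observed odds ratio follows from the two groups. The true odds ratio is set to 1.

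With equal error in both groups (Se 0.90, Sp 0.95), the observed odds ratio is 1.00.

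Next, Se is 0.90 in both groups, with Sp 0.90 in one and 0.95 in the other. At p = 0.10:

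- Sp 0.90: 0.10 × 0.90 + 0.90 × 0.10 = 0.180
- Sp 0.95: 0.10 × 0.90 + 0.90 × 0.05 = 0.135
- Odds ratio: (0.180/0.820)/(0.135/0.865) = 1.41, or its reciprocal 0.71 if C2 is the group that over-reports

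| True prevalence | Exposed group over-reports | C2 over-reports |
|---|---|---|
| 5% | 1.60 | 0.63 |
| 10% | 1.41 | 0.71 |
| 20% | 1.25 | 0.80 |
| 30% | 1.17 | 0.85 |

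A sensitivity difference alone matters less. Se 0.95 in the exposed group against 0.85 in C2, with Sp 0.95 in both, gives 1.06 at 5% prevalence and 1.15 at 30%.

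**Step 3: the campaign.** It names C2 as well as W2, F and C1, so it does not separate exposed from control. The only group not named is W1, which is 50 of the 150 workers. Suppose the campaign multiplies the odds of reporting by k everywhere except W1, with no true effect. For k = 1.5 and baseline 10%:

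- Campaign groups: odds 0.1111 × 1.5 = 0.1667, prevalence 0.1429
- Workers: (100 × 0.1429 + 50 × 0.10)/150 = 0.1286, odds 0.1475
- Odds ratio, workers against C2: 0.1475/0.1667 = 0.885

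For k = 1.2 the result is about 0.94, and for k = 2.0 it is 0.81 to 0.82 (baselines 10% and 20%). Any such effect lowers the worker odds ratio.

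**The case against.** The strongest reply is that the plan already puts the chapters most openly about risk after the symptoms: risk perception, protective equipment and worker safety. This is correct. The symptom questions are also partly anchored. Diarrhoea has a stool-count definition and set time points, skin disease is asked by body site, and skin and eye disease follow a handbook. The sample size rests on intestinal parasitic infection and Hypothesis 2 on egg counts, so the main quantitative case does not depend on symptoms.

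A second reply is that chapter order cannot remove what participants know about their own job, what they learn at consent, or what the interviewer knows about the group. That also stands, and it limits what reordering can achieve.

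A third is that the evidence is incomplete. The questionnaire is a separate annex, the form will be refined after pre-testing, and the timetable shading is not visible. Question order here rests on chapter numbering, and campaign timing on row order.

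None of this removes the remaining point: chapter 2 comes before the symptoms and is not the same for all groups.

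**Conclusion.** The symptom odds ratios are open to differential reporting, and part of that opening is an avoidable feature of question order. The size and net direction are unknown. The tables above show what assumed error rates would do and do not estimate bias in this study.

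Three stronger readings are tempting, and the documents do not support them.

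- A reader might infer that priming inflates the exposed groups' odds ratios. For instance, if 2% to 5% of symptom-free exposed participants reported a symptom and C2 did not, a true odds ratio of 1 would appear as 1.10 (2% at 20% prevalence: 0.20 + 0.80 × 0.02 = 0.216) up to 1.53 (5% at 10% prevalence: 0.10 + 0.90 × 0.05 = 0.145). But C2 is named for the campaign and is asked the swamp items, so an unprimed C2 does not fit the plan. Nor could such a figure be attributed to question order alone.
- A reader might infer that the campaign biases exposed against control. It covers both, its content is not described, and W1 is sensitised by another route.
- A reader might infer that biased diarrhoea data will be used to validate the simulated risks. The Abstract and section 1.4 are loose enough to allow that, but section 4.2.3.1 names only the parasitic infection data.

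The point is therefore a worthwhile free improvement and leaves the stool-based analyses untouched.

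**What to change.** - Move chapter 6 to directly after chapter 1, ahead of chapters 2 to 5. Leave chapters 7 to 9 where they are, after symptoms. Fix this order in the ODK form before pre-testing.
- Describe the content of the pre-survey information and use the same content in all five groups, including W1. Do not hold back anything participants must be told for consent.
- Report the symptom odds ratios as self-reported, alongside the stool-based results, and state that reporting may differ by group.

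The cost is small, because section 4.2.1.7.2 shows that the form has still to be translated, coded and adjusted after pre-testing. If the questionnaire annex has already gone to the ethics committees, the reordered version would need to be sent to them. The change removes cueing within the interview only. Knowledge of one's own job, consent information and the interviewer's awareness of the group remain, and should be named as limitations.
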